**vi) Randomization and treatment assignment and allocation**

Schools will be randomly assigned to one of the four intervention groups using a pre-defined stratified randomization procedure. A computer generated randomization list will be created by a member of the project who will not be directly involved in the conduct of the study. Sealed copies of the original randomization lists and documentation of the procedure used to generate the lists will be stored in KEMRI offices in Nairobi. Prior to the onset of the study, sealed copies of the randomization lists will be distributed to the member of the study team responsible for treatment allocation.

Schools will be stratified into five groups according to school examination performance in previous years, to account for differences in school quality and socio-economic environment. Five schools will be randomly selected from each school-performance stratum, and within each stratum schools were randomly allocated to 1 of 5 coded drug groups using block randomization according to the randomization listing.

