**vii) Study interventions**

In this study, two interventions will be provided: i) intermittent screening and treatment (IST) for malaria and ii) a programme of training for primary school teachers to improve literacy instruction.

The malaria prevention strategy will involve all children being screened using rapid diagnostic tests (RDTs) for malaria once a term (thrice yearly). Children (with or without malaria symptoms) found

to be RDT-positive will be treated with artemisinin-based combination therapy (ACT). Screening and treatment will be administered by district health workers once a school term, observed by the evaluation research team.

An education intervention will be conducted in half of the schools receiving IST and half of the control schools. The intervention is designed to improved early grade literacy instruction. Recent evidence (Snow et al., 1998) suggests that relatively simple steps can be taken by teachers in order to improve the development of children's literacy in the early grades. It is particularly important to develop students' oral language skills (e.g., phonological awareness & vocabulary) and to teach the relationship between letters and sounds in a systematic and explicit fashion. Such instructional techniques are encouraged in the current Kenyan curriculum but teachers face many challenges in implementing them systematically and effectively. The aim of the instructional intervention will be to support teachers in implementing these teaching methods. Specific interventions will be design based on further consultation with all stakeholders and ongoing class observations in Kwale but may include training on (i) how to monitor students' progress in large classes (ii) developing and using instructional materials for reading (iii) lesson planning for explicit teaching of letter-sound relationships (iv) instructional techniques for large classes.

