#### **Data analysis**

All analyses will be on the basis of intention-to-treat. To assess the success of randomization baseline characteristics between the four randomization groups will be compared. To assess the impact of the interventions, methods appropriate for cluster-randomized trials will be used (Hayes & Bennett, 1999). The prevalence, or mean, in each school will be calculated and the unadjusted risk ratio (RR), or mean difference (intervention-control), estimated in each stratum. An overall estimate of the effect of IST will be obtained by taking a weighted average of the stratum-specific estimates, the weights proportional to the number of schools per stratum, and 95% confidence intervals will be adjusted for observed between-school variance. Formal hypothesis testing will be undertaken using stratified unpaired t-tests. The impact of each intervention will be estimated for education outcomes and health outcomes in separate multiple regression models. An interaction term will be included to identify any synergistic effects between the two interventions. Statistical analysis will be carried out using STATA® software, version 10.0. (Stata Corporation, Texas, USA).

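### The formal IST test pools literacy-trained and untrained schools within examination strata, so its confidence interval on the education primary outcome is modestly too wide

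*Protocol*

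**What the plan says.** Protocol section 9 (Data analysis) sets out the IST comparison in steps. School prevalences or means are calculated, with "the unadjusted risk ratio (RR), or mean difference (intervention-control), estimated in each stratum". Then "An overall estimate of the effect of IST will be obtained by taking a weighted average of the stratum-specific estimates", with weights proportional to the number of schools per stratum. Of the interval and the test it says: "95% confidence intervals will be adjusted for observed between-school variance. Formal hypothesis testing will be undertaken using stratified unpaired t-tests".

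The strata come from section 8(vi): "Schools will be stratified into five groups according to school examination performance in previous years". No other stratification factor is named.

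Section 8(vii) describes the factorial structure: "An education intervention will be conducted in half of the schools receiving IST and half of the control schools".

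After the t-test sentence, section 9 adds: "The impact of each intervention will be estimated for education outcomes and health outcomes in separate multiple regression models", with an interaction term between the two interventions. It does not say how these models rank against the t-tests.

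**The concern.** Within an examination stratum, both the IST side and the non-IST side contain schools with and without literacy training. If the training raises scores, the trained and untrained schools on the same side have different means. A variance computed across all schools on that side counts this planned difference as random between-school variation.

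Because the literacy arms are balanced across IST, the literacy effect cancels from the IST contrast and adds nothing to its true sampling variance. Only the estimated variance grows. The interval is then wider than it needs to be, and the test rejects less often than its nominal level.

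This matters for the second primary outcome, educational achievement, because the literacy intervention is meant to move part of it. The better the training works, the less sensitive the formal IST test becomes.

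**Working it through.** **Does the plan pool over literacy?** The anaemia sample size in section 8(v) answers this. The inputs are 20% v 15%, 80% power, 5% level (two-sided assumed), ICC 0.025 and 50 children per school.

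- Individuals per side: 906.
- Design effect: 1 + 49 × 0.025 = 2.225.
- Schools per side: 906 × 2.225 / 50 = 40.3, plus 1 = 41.3, rounded up to 42.
- Total: 84 schools, or 21 per factorial arm, which is the Protocol's figure.

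Power is about 82% for 42 v 42 schools but only about 53% for 21 v 21. The stated figure therefore works only if IST is compared across both literacy levels.

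**Inputs for education**

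- From section 8(v): 100 schools, 50 children per school, ICC 0.2 (reported range 0.1 to 0.2), effect size 0.2 SD, baseline-to-final correlation 0.7.
- Assumed: an even layout of 5 strata × 4 arms × 5 schools; no interaction; a literacy effect L. The Protocol gives no separate value for L, so 0.2 SD is used, with a range from 0 to 0.4 SD.

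**Correct standard error.** The variance of a school mean is V = 0.2 + 0.8/50 = 0.216 SD². With 50 v 50 schools, SE = √(2 × 0.216/50) = 0.0930.

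**Standard error as written.** Each stratum-by-IST cell has 10 schools, five at +L/2 and five at −L/2 around the cell mean. On average this adds 10 × (L²/4) / 9 = (10/9)(L²/4) to the sample variance. For L = 0.2:

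- V becomes 0.216 + (10/9)(0.01) = 0.2271.
- SE = √(2 × 0.2271/50) = 0.0953.
- Ratio: 0.0953/0.0930 = 1.025.

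**Degrees of freedom.** Pooled: 5 × 2 × 9 = 90 (critical t 1.987). Split by literacy arm: 5 × 4 × 4 = 80 (critical t 1.990).

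**Results for V = 0.216.** The SE excess is from the formula. Type I error and power for a 0.2 SD IST effect are from simulation, 100,000 runs per scenario.

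| L (SD) | SE excess | Type I error, as written | Power, as written | Power, split by literacy arm |
|---|---|---|---|---|
| 0 | 0% | 4.9% | 56.9% | 56.7% |
| 0.2 | 2.5% | 4.4% | 54.7% | 56.6% |
| 0.3 | 5.6% | 3.9% | 52.3% | 56.7% |
| 0.4 | 9.8% | 3.2% | 49.0% | 56.6% |

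Repeat simulations at L = 0.2 gave type I errors of 4.5% and 4.6%, so about 4.5% is a fair summary.

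**Sensitivity at L = 0.2**

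- ICC 0.1: V = 0.1 + 0.9/50 = 0.118; SE excess 4.6%; power 79.5% as written v 81.9% split.
- Baseline-adjusted school means: V = 0.216 × (1 − 0.49) = 0.110; SE excess 4.9%; power 82.3% v 84.5%. The test in section 9 is unadjusted, so this does not describe it.
- V = 0.216 takes no credit for variance absorbed by the examination strata. Any absorption raises the relative SE excess, as the smaller V values show.

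**The case against.** The strongest reply is that the remedy is already in the same paragraph. A regression containing both interventions removes the literacy effect from the residual, and section 8(i) also describes these models. This stands in part: the means of correction exist. But section 9 attaches formal hypothesis testing to the t-tests and the interval to the stratum-averaged estimate, and gives the regression no governing status.

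Second, pooling is inferred. Section 8(i) assigns the evaluation of IST to the first two arms, which would not be a four-arm comparison. That sentence does conflict with the rest. As the arms are listed, the first two are IST alone and education alone, which is not a usable IST contrast. The 84-school figure supports pooling. The conflict still has to be resolved.

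Third, the five-schools-per-cell layout is not stated. Section 8(vi) describes five schools per stratum and five coded drug groups, which does not match four arms and 100 schools. The layout is therefore an assumption. It affects the 10/9 factor and the degrees of freedom, not the direction.

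Fourth, t-test cells are often left to a statistical analysis plan, and section 8(xii) foresees an analysis plan approved by the DSMB. That would excuse silence, but here the Protocol has itself fixed the test and its strata.

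Fifth, the reach is limited. The Protocol gives no reason for literacy training to change anaemia, and the education battery includes arithmetic, which the training does not target. Both points stand.

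**Conclusion.** The point holds, at modest size. As written, the formal IST test and interval on the education primary outcome carry about L²/4 of literacy effect in the variance. The estimate is unbiased and the error is conservative. At 0.2 SD, the only education effect size the Protocol uses for its achievement tests, the SE is about 2.5% too large and about 2 power points are lost. This rests on the even layout, ICC 0.2, no interaction, and a literacy effect equal to the design value.

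A reader might infer that a null IST result on education could be produced by this choice. The documents do not support that. On the unadjusted test, power for 0.2 SD is only about 57% even after the correction, and pooling moves it by about 2 points at the design value. The larger gap, between 57% and the roughly 85% obtained with the 0.7 baseline correlation, comes from the test being unadjusted, which is a separate matter.

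A reader might also cite a fall in power from about 85% to 75%. That needs a 0.4 SD literacy effect, which appears nowhere in the Protocol, together with a baseline adjustment that this test does not make.

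**What to change.** In section 9 (Data analysis), make the formal IST analysis account for literacy arm in one of two ways:

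- **Stratify the t-test.** Define its cells, and the variance behind the interval, by examination stratum × literacy arm. On the assumed layout this gives 10 strata of 5 v 5 schools.
- **Name the regression.** State that the model with examination stratum and both interventions supplies the formal test and the interval. Take the main IST effect from the model without the interaction, or code the arms −½ and +½. With 0/1 coding and the interaction included, the IST coefficient is the effect in untrained schools only, which is a 25 v 25 comparison with SE √(2 × 0.216/25) = 0.131.

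Treat the literacy effect in the same way, by IST arm. In section 8(i), reconcile the sentence on the first two arms with the pooled factorial comparison.

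The stratified version costs 10 of 90 degrees of freedom. That raises the critical t from 1.987 to 1.990, about 0.2% of interval width. With no literacy effect, simulated power is 56.7% against 56.9%. No new data are needed.

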**v) Sample size determination**

Power analysis was adjusted for clustering (Hayes & Bennett, 1999) and focused on two main outcomes of interest: the percentage of children who are anaemic (haemoglobin <110 g/L); and education achievement assessed by a battery of tests of reading, writing and arithmetic.

For anaemia, assuming a baseline prevalence of 20% (as found in the 2008 school surveys in Kwale), an intraclass correlation of between 0.025 and 50 children sampled per school, a sample size of 21 schools with a total of 1050 children of all ages in each arm was estimated to provide 80% power to detect a 25% reduction in anemia in the intervention group compared to placebo at 5% level of significance. This equates to 84 schools and 4200 children.

For educational achievement tests, an overall sample size of 100 schools with 50 children per school (5000 children overall) is sufficient to detect an effect size of 0.2 standard deviation (SD) assuming an intra-class correlation of 0.2 (ICC varied from 0.1 to 0.2 with mathematics and literacy tests in Class 2 in 210 schools in Western Kenya; ICC is expected to be lower in Class 1) and a correlation between baseline and final test scores of 0.7. This sample size is sufficient to detect an effect size of 0.15 SD for concentration tests, which have a lower intra-class correlation (0.07 in the previous study in Bondo).

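### The education sample size relies on a baseline–final correlation of 0.7, but the formal test named in the protocol does not use the baseline score, and no baseline-adjusted analysis is identified as primary

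*Protocol*

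**What the plan says.** **Sample size (Protocol, section 8 v).** For educational achievement, 100 schools with 50 children each are described as "sufficient to detect an effect size of 0.2 standard deviation (SD) assuming an intra-class correlation of 0.2", together with "a correlation between baseline and final test scores of 0.7". The ICC has a stated source: "ICC varied from 0.1 to 0.2 with mathematics and literacy tests in Class 2 in 210 schools in Western Kenya". The text adds that a lower ICC is expected in Class 1. No power or significance level is attached to the education calculation. Those appear only for anaemia: "80% power to detect a 25% reduction in anemia in the intervention group compared to placebo at 5% level of significance".

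**Analysis (Protocol, section 9, Data analysis).** A prevalence or mean is calculated for each school, with "the unadjusted risk ratio (RR), or mean difference (intervention-control), estimated in each stratum". The stratum estimates are combined with weights proportional to the number of schools. Then: "Formal hypothesis testing will be undertaken using stratified unpaired t-tests". The next sentences say that the impact of each intervention on education and health outcomes will be estimated in separate multiple regression models, with an interaction term. The covariates in those models are not named, and nothing says whether the t-test or the regression is primary. Section 8 i also describes the analysis as multiple regression and does not mention a t-test.

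**Data available (Protocol, section 8 ix).** A school performance test is planned before treatment for the study cohort, starting in standard 1. The same section says that covariates can raise power considerably.

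**The concern.** A correlation between baseline and final scores reduces the required sample size only if the analysis removes the variance that the baseline score explains, by adjustment or by a change score. The sample size section takes that reduction. The one procedure that the analysis section calls formal hypothesis testing works on unadjusted school means and gives the baseline score no role. If the education test were run as written, it could fall well short of the sensitivity that the 100 schools were meant to buy.

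Educational achievement is one of the two primary outcomes (section 8 ii). The background (section 4 b) reports that the earlier trial in western Kenya improved sustained attention but not achievement. A second null result on achievement would be hard to interpret if the deciding test lacked power.

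**Working it through.** **Inputs**
- Children per school m = 50, 100 schools, effect 0.2 SD, ICC 0.2, correlation r = 0.7 (section 8 v).
- k = 50 schools per side for each main effect, assuming four equal groups. Section 8 vii supports this: "An education intervention will be conducted in half of the schools receiving IST and half of the control schools". Section 15 puts the literacy intervention in 50 schools.
- Assumed: a two-sided 5% level, and 80% power as the benchmark, since section 8 v gives neither for education.

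**Formulas** (outcome in SD units)
- Variance of a school mean: V = ICC + (1 − ICC)/m = 0.2 + 0.8/50 = 0.216. The design effect is 1 + 49 × 0.2 = 10.8, and 10.8/50 = 0.216.
- SE of the difference: √(2 × V × f / k).
- f = 1 if baseline is ignored; f = 1 − 0.7² = 0.51 with baseline adjustment; f = 2(1 − 0.7) = 0.60 for a change score. The last two take r = 0.7 to hold both between and within schools.
- Power = Φ(0.2/SE − 1.96). Effect detectable with 80% power = 2.80 × SE.

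**Reproducing the plan's figure**
- Baseline adjustment: SE = √(2 × 0.216 × 0.51/50) = 0.0664. Power 85.4%, detectable effect 0.186 SD, about 87 schools needed for 80% power.
- Change score: SE = √(2 × 0.216 × 0.60/50) = 0.0720. Power 79.3%, detectable effect 0.202 SD, about 102 schools needed.

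The statement that 100 schools suffice is therefore reproduced for a factorial main effect, provided the baseline score is used.

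**Baseline ignored**
- SE = √(2 × 0.216/50) = 0.0930. Power 57.6% (56.8% with the t-distribution), detectable effect 0.26 SD. Power of 80% at 0.2 SD would need about 85 schools per side, 170 in total.

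**How far 57.6% can move without the baseline score**

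| ICC | Share of between-school variance explained by strata (assumed) | V | SE | Power at 0.2 SD |
|---|---|---|---|---|
| 0.20 | 0 | 0.216 | 0.0930 | 58% |
| 0.20 | 20% | 0.16 + 0.016 = 0.176 | 0.0839 | 66% |
| 0.20 | 30% | 0.14 + 0.016 = 0.156 | 0.0790 | 72% |
| 0.15 | 0 | 0.15 + 0.017 = 0.167 | 0.0817 | 69% |
| 0.15 | 30% | 0.105 + 0.017 = 0.122 | 0.0699 | 82% |
| 0.10 | 0 | 0.10 + 0.018 = 0.118 | 0.0687 | 83% |

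At ICC 0.2, 80% power needs V = 0.1274. The strata would then have to explain 1 − (0.1274 − 0.016)/0.2 = 0.44 of the between-school variance. The protocol gives no value for this share.

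**The case against.** The strongest reply is that the protocol already plans an analysis that could carry the baseline score. Sections 8 i and 9 both specify multiple regression for education outcomes, section 8 ix plans the pre-treatment test and says why covariates are collected, and section 8 xii refers to an analysis plan to be approved by the data safety monitoring board. Naming covariates can be left to that plan.

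Much of this stands. A reader might infer that the t-test alone decides the education answer, but the document does not say so; it leaves the primary analysis open. A missing covariate list is not the fault. What remains is that the only procedure labelled formal hypothesis testing is an unadjusted one, while the sample size assumes otherwise.

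Three further replies limit the size of the point.
- A reader might take 58% as the power of the trial. It is not. It uses the top of the quoted ICC range, although a lower ICC is expected in Class 1, and it gives no credit for strata built on past school examination performance (section 8 vi), a plausible predictor of achievement.
- A reader might conclude that only covariance adjustment reaches 0.2 SD. A change score also uses the 0.7 correlation and comes closer to the stated 100 schools. Section 9 does not say whether the school mean is of final or change scores, although no change from baseline is mentioned.
- No power is stated for education, so falling short of 80% is measured against an assumed benchmark.

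**Conclusion.** The mismatch is real and should be fixed. The education sample size spends a gain from the baseline score that the named formal test does not collect, and the regression that might collect it is not identified as primary.

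At the protocol's own planning ICC of 0.2, ignoring baseline costs about 28 percentage points of power against adjustment (85.4 − 57.6) before any gain from stratification. With modest stratification gains or a lower ICC the loss is smaller, and at ICC 0.1 unadjusted power still exceeds 80%. The document does not fix where in this range the trial lies.

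These figures rest on a two-sided 5% level, 50 v 50 schools, and r = 0.7 holding for school means as well as within schools. The school-level part matters most: if baseline explained only within-school variance, V would be 0.2 + 0.016 × 0.51 = 0.208 and power about 59%.

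A reader might also infer that the planned test is invalid. The documents do not support that: a cluster-level t-test respects the unit of randomisation and is merely less efficient. This is why the point is a should-fix and not a must-fix.

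**What to change.** In Protocol section 9, Data analysis, name the primary formal test for educational achievement and make it baseline-adjusted. Either form would do:

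- **Two stages:** regress the final score on the child's baseline score and stratum, without the intervention terms, then apply the t-test to the school mean residuals.
- **One model:** a regression or mixed model with a school random effect, stratum and baseline score. If the planned multiple regression was always meant to be primary, one sentence saying so and naming the baseline score is enough.

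Keep the unadjusted stratified t-test as a supportive analysis. In section 8 v, it would help to state the power and significance level assumed for education and how the 0.7 correlation enters the calculation.

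The cost is analysis wording only. The pre-treatment test is already planned, and neither the number of schools nor data collection changes.

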### **10. Time Frame**

|                                                        |     |     |     |     |     |     |     |     |     |     |     |     |
|--------------------------------------------------------|-----|-----|-----|-----|-----|-----|-----|-----|-----|-----|-----|-----|
| 2008                                            |     |     |     |     |     |     |     |     |     |     | Nov | Dec |
| Staff recruitment and training                         |     |     |     |     |     |     |     |     |     |     |     |     |
| Development and piloting of education assessment tools |     |     |     |     |     |     |     |     |     |     |     |     |
| 2009                                            | Jan | Feb | Mar | Apr | May | Jun | Jul | Aug | Sep | Oct | Nov | Dec |
| Development and piloting of education assessment tools |     |     |     |     |     |     |     |     |     |     |     |     |
| Teacher training workshop                              |     |     |     |     |     |     |     |     |     |     |     |     |
| Baseline health and education surveys                  |     |     |     |     |     |     |     |     |     |     |     |     |
| IST                                                    |     |     |     |     |     |     |     |     |     |     |     |     |
| Instruction intervention                               |     |     |     |     |     |     |     |     |     |     |     |     |
| Assessment of class behaviour                          |     |     |     |     |     |     |     |     |     |     |     |     |
| 2010                                            | Jan | Feb | Mar | Apr | May | Jun | Jul | Aug | Sep | Oct | Nov | Dec |
| First follow-up health and education surveys           |     |     |     |     |     |     |     |     |     |     |     |     |
| IST                                                    |     |     |     |     |     |     |     |     |     |     |     |     |
| Instruction intervention                               |     |     |     |     |     |     |     |     |     |     |     |     |
| Assessment of class behaviour                          |     |     |     |     |     |     |     |     |     |     |     |     |
| First follow-up health and education surveys           |     |     |     |     |     |     |     |     |     |     |     |     |

